## Abstract

**Introduction:**

The current COVID-19 pandemic has forced hospices to look for more ways to support people remotely, including psychological support. Emotional disclosure-based interventions hold potential as a way of providing support remotely. However, evidence of their efficacy in people with terminal illness is mixed. Reviews have highlighted this may be due to interventions not being tailored to the unique needs of this population. In response to this, we are developing Let It Out (LIO), an online, self-guided emotional disclosure-based intervention tailored for people living with terminal illness.

**Aims:**

The primary objective of the study is to optimise the design of the LIO intervention. Secondary objectives include assessing its acceptability and feasibility; exploring potential impact on well-being; identifying potential adverse effects; and informing choice of outcome measures for potential future evaluation.

**Methods and analysis:**

A single arm, mixed-methods, multisite, longitudinal study. Up to 40 people living with a terminal illness under the care of hospices in England and Scotland will receive the online LIO intervention. LIO consists of 3, self-guided expression sessions over 2 weeks. The primary outcome measures are (1) a structured feedback form completed by participants after the final expression session; and (2) semi-structured interviews and focus groups with ≤15 patient participants, ≤30 hospice staff and ≤15 informal carers. These quantitative and qualitative data will be triangulated via process evaluation to inform optimisation of the intervention design. Secondary outcome measures include validated measures of physical and psychological health collected at baseline and after the final expression session (immediately, 1, 4 and 8 weeks after); and data on recruitment, retention and fidelity.

**Ethics and dissemination:**

The study is approved by the University College London Research Ethics Committee (reference: 15281/002). The findings will be shared through peer-reviewed scientific journals and conferences, and traditional, online and social media platforms.

Strengths and limitations of this studyThe Let It Out intervention has been developed based on evidence from a scoping review of previous research, and refined drawing on insights from testing it in a slightly different form in another population and feedback from key stakeholders.The acceptability and feasibility of the intervention will be explored using a rich, mixed-methods approach, using process evaluation to triangulate quantitative recruitment, retention and acceptability data with qualitative written and interview feedback.Recruitment may be restricted by the relatively short recruitment period and potential limitations on hospice staff capacity (due to COVID-19 related pressures on hospice teams).The study is taking place during a time of transition and ongoing change in methods of care, necessitated by the evolving COVID-19 pandemic that may restrict generalisability of the findings outside of this context.This is a single-arm study not designed to formally evaluate efficacy of the intervention.

## Introduction

People living with terminal illness carry a unique emotional burden and can experience significant distress.^1–4^ Psychological support is a key part of the holistic care provided by hospices and other palliative care services.^5–8^ But evidence suggests psychological service provision at the end-of-life is currently inadequate, and services are often under-resourced and overburdened.^9–11^ Since the start of the COVID-19 pandemic in early 2020, hospice funding and capacity have been placed under even more threat.^12^ Hospices are increasingly turning to telehealth approaches to deliver care to patients.^13^ At present this is necessary to help minimise face-to-face contact in line with recommended social distancing practices that are particularly crucial for this vulnerable population.^14^ However, delivery of care using such methods is potentially cost-effective and time-effective, and if found to be beneficial, may endure beyond the resolution of the pandemic to help broaden access to palliative care.

Emotional disclosure (ED)-based therapies, such as expressive writing or talking, are easy to implement as a means of support, with minimal requirement for staff supervision and potential to be delivered online.^15 16^ The traditional expressive writing protocol is based on the principle that expressing feelings about personal, traumatic experiences can provide comfort.^17^ Indeed, there is evidence that such interventions can provide psychological and physical benefits in healthy populations.^18^ Expressive writing has also been adapted, to include, for example, disclosing about positive events,^15 19 20^ writing or talking about stress from a compassionate stance^21–23^ or writing about future goals.^24 25^ Writing from a compassionate stance has been shown to reduce negative affect^22 26^ and improve mood.^27^ However, evidence of benefit of ED-based interventions in palliative populations is more mixed.^28 29^ The mixed results may be because there has been a lack of research into developing an ED-based intervention tailored to the specific needs of this population.^28^ The underlying causal mechanisms, and thus the outcome measures that may be most suitable to capture any potential benefit of such an intervention in this population, also remain unclear.

Based on this gap in the literature, our group conducted a scoping review of ED-based interventions in people with terminal illness.^29 30^ The review aimed to identify potentially effective characteristics of interventions for this population to inform the development of a tailored ED-based intervention. The review identified 25 relevant primary studies, but found that quantitative evidence was not available to determine which, if any, characteristics may be most effective. However, the qualitative analysis of authors’ experiences of testing the interventions highlighted a number of themes that may be important to consider when developing an ED-based intervention for people with terminal illness. These include flexibility of when, where and how to complete the intervention, clarity of instructions and provision of a safe environment for disclosure.

Building on the results of this scoping review, we developed an ED-based intervention in collaboration with key stakeholders named Let It Out (LIO). We then refined its design by incorporating insights from a trial we ran of an adapted version of the intervention tested in the general population during the COVID-19 pandemic,^31^ and further stakeholder feedback. This study represents the next phase of the intervention development process.

### Aims and objectives

The primary objective of the study is to optimise the design of an ED-based intervention (LIO) tailored for people receiving palliative care from a UK hospice. The secondary objectives are to:

Assess whether the intervention and study procedures are acceptable and feasible in UK hospice services.Explore the potential impact of the intervention on psychological and physical well-being, and identify any potential adverse effects.Inform the choice of outcome measures and study design for possible future large-scale intervention evaluation.Explore the causal mechanisms underlying potential intervention efficacy.

An exploratory objective is to explore the core concerns of people following referral to hospice care. This is one of the topics covered in the intervention expression sessions; responses could potentially inform strategies to minimise or address those concerns.

## Methods and analysis

### Design

A pragmatic, single-arm, multisite, mixed-methods longitudinal study. The study design has been developed in line with the latest Medical Research Council (MRC) guidelines,^32 33^ which recommend an iterative intervention development and evaluation process. Mixed-methods, pragmatic study designs are recognised as an appropriate way for researchers to approach the development and evaluation of complex interventions in palliative care.^34^ We are employing a convergent design to integrate quantitative measures of fidelity, feasibility, acceptability and possible impact, with semi-structured interviews and focus groups. In the qualitative aspect of the study, we will take a phenomenological approach to capture more nuanced feedback on the participants’ experience of the intervention, including their views on its design, acceptability and any perceived effects.^34 35^ The quantitative and qualitative data will be integrated through a process evaluation. As the focus of the study is on applying pragmatic mixed-methods to optimise intervention design, this study will not formally evaluate nor test *a priori* hypotheses regarding its efficacy or report p-values.

The study is approved by the University College London Research Ethics Committee (reference: 15281/002).

### Setting

The study will take place in six hospice services across England and Scotland. A list of participating sites is available from the authors.

### Participants

The study will be conducted in three population groups recruited from participating hospices:

#### Group 1

Up to 40 adults living with terminal illness receiving palliative care from a UK hospice (on an inpatient, day care, outpatient or community basis). A sample size of 40 is recognised by the National Institute of Health Research as being appropriate for intervention feasibility and pilot work that is not designed to evaluate efficacy.^36 37^

##### Group 1 exclusion criteria

Not expected to survive for longer than 10 weeks (based on clinical judgement).Lack of capacity to give informed consent or may be expected to lose capacity to give informed consent within 10 weeks (based on clinical judgement).Known diagnosis or history of severe depression, suicidal tendencies, psychotic symptoms, severe mood disorders, mania, schizophrenia, psychopathic/borderline personality disorder, severe and episodic (type 1) bipolar (affective) disorder (that is not well controlled).Not able to understand and communicate in English.

#### Group 2

Up to 15 informal (adult friend or family) carers of Group 1 participants.

#### Group 3

Up to 30 paid or voluntary hospice staff involved in organisation, delivery or implementation of psychological and/or emotional support.

### Recruitment

#### Group 1

We will employ convenience sampling. This is a pragmatic decision based on difficulties recruiting participants during the COVID-19 pandemic; the target numbers for recruited participants are in place to manage the scope of the research. We will assess recruitment rate as part of the study’s feasibility assessment. The recruitment window has been selected based on research team capacity and funding availability.

Clinical and research staff at hospice sites will identify patients who may be eligible to participate between October 2020 and January 2021. They will make initial contact, explain the study and if the participant is interested, provide them with an invitation letter, email or link to the study website. The study website hosts the participant information sheet and a link to an online reply form. Participants can indicate on the reply form if they would or would not like to take part.

If participants select yes on the reply form, they can progress to the online informed consent and advance consent form, which asks what participants would like to happen to their data if they lose capacity over the course of their participation in the study. If they select no, they have the option to provide their reasons for not taking part. There is also an option to request further information from the research team before making a decision. If participants select this option, they are prompted to provide their contact details and a member of the research team will phone or email them to discuss the study further. If, having discussed the study, participants choose to take part, they can progress to the online informed consent and advance consent forms. The research team will inform the relevant hospice when a participant from their service consents to take part, so it can be recorded on their patient notes. The participant will be reminded of their right to withdraw from the study at any time throughout the study in online materials and through direct communication with the research team.

In the initial phase of the study, all Group 1 participants will be invited to take part in a semi-structured interview. Depending on uptake, once a third (n=5) have been recruited to interview phase, we will assess the mix of participants in terms of demographic characteristics, to inform recruitment targets according to a purposive sampling framework.

#### Group 2

Informal carers will be recruited through researcher contact with Group 1 participants. If their carer indicates they may be interested in taking part in an interview, the research team will arrange a time to discuss the study; if interested in taking part, they will be sent a link to the online participant information sheet and informed consent form.

#### Group 3

Staff and volunteers will be recruited through liaison with clinical leads at each hospice site. The research team will approach eligible staff members to introduce the study, and if interested, provide them with a link to the online participant information sheet and informed consent form.

The study will be presented at hospice staff team meetings and internal newsletters to support recruitment.

### The intervention

#### Development

The LIO intervention has been developed in collaboration with a group of stakeholders, including psychologists, a psychiatrist, palliative care and hospice staff, palliative care specialist researchers and patient and public involvement (PPI) representatives. The intervention was first developed based on the findings of a scoping review of related interventions conducted by the research team.^29^ Based on the review findings, the LIO intervention is flexible in terms of when, where and how it can be completed; provides clear, structured instructions; and emphasises the importance of completing sessions in a safe, comfortable setting. During the COVID-19 pandemic, the research team adapted the intervention to test its effect on distress in the general population during the pandemic (the Let It Out - COVID-19 response [LIO-C] study).^31^ Based on feedback from participants in that study, adaptations were made to LIO to minimise any potential risk of causing short-term distress; namely, by incorporating clearer directions on how to express feelings with self-compassion.

#### Theoretical basis

The intervention development process has been guided by emotion regulation theory, which posits that the active component of ED-based interventions is the emotional arousal following expression of emotions.^38–40^ This account suggests that one is able to develop acceptance of their thoughts and feelings through mastery, self-efficacy and control of their emotions. This account also sits within theories underlying positive psychology and self-compassion interventions,^19 41^ which propose that one is able to gain a better understanding of the emotions associated with their experiences by learning how to more helpfully structure thoughts and feelings. We recognise that there is unlikely to be a single process underlying ED; indeed, several alternative processes have been proposed to explain ED including emotional inhibition, cognitive adaptation and exposure.^42–45^ One aim of this study, in line with the MRC complex intervention development guidance,^33^ is to explore the mechanisms through which LIO may be effective.

#### Outline

LIO is a self-guided intervention designed to enable people living with terminal illness to self-compassionately express their feelings in a way that may help to bring them comfort. In this study, participants will be sent a link to online intervention instructions, as well as a PDF intervention guide that can be downloaded from the online survey platform. The guide provides instructions for participants to work through the study and intervention. Over 2 weeks, participants are asked to express their feelings in a self-compassionate way in response to prompts in 3 separate, 20–30 minute ‘expression sessions’. Figure 1 presents the general instructions given to participants to use across each session and the prompts for each session.

**Figure 1 F1:**
[figure not shown]
General instructions and session specific prompts as part of Let It Out guide (written version).

Participants are advised to complete sessions in a comfortable place, and, if possible, in private (although it is recognised this may not be feasible or wanted for all participants). Participants can handwrite, type or audio-record (using their personal mobile phone or laptop) their response to the prompts. There are 2 guides: one for those choosing to write, the other for those choosing to audio-record. The full guides are available on reasonable request from the authors.

To make the intervention as accessible as possible, it is acceptable for participants to have support from a carer to help complete the expression sessions, and the associated questionnaires. This help can be delivered in any way that works best for the participant. The guide and website include signposts to other helpful resources that can support mental well-being. The guide also provides a space for participants to plan when and where they will complete each session, based on the theory of action planning to help bridge the intention-behaviour gap.^46^

### Data collection

#### Overview—group 1

Table 1 provides a detailed description of the participant timeline and outcome measures for Group 1 participants.

**Table 1 T1:** Group 1 participant timeline, outcome measures and analysis approach

Measure	Time points administered	Description	Data type	Analysis approach	Relevant research objective*
Demographics	Baseline	Approximate date of hospice referral, age, gender, ethnicity, marital status, religious background, level of education, type of care (eg, inpatient, outpatient, day care), diagnosis, mental health history and COVID-19 status.	Quantitative	Descriptive statistics	1. Feasibility and acceptability
Expression sessions	Three sessions over 2-week intervention period	Typed, handwritten or audio-recorded responses to three expression sessions that make up the LIO intervention.	Quantitative and qualitative	LIWC and BIR inductive thematic analysis (session 2)	Feasibility and acceptability Underlying mechanisms Exploratory objective (session 2)
Health-related outcome measures (see below for details)	Baseline, immediately after the final expression, and, 1 week, 4 weeks and 8 weeks after the final expression	See below for details.	Quantitative	Descriptive statistics and descriptive pre–post analysis	Feasibility and acceptability Impact on well-being Outcome measure selection Underlying mechanisms
Integrated Palliative Care Outcome Scale (IPOS)—patient version^56^		An updated, brief (10 questions, 17 items) version of the POS instrument. IPOS was developed specifically to capture a range of the most important concerns of people living with palliative-stage disease, covering symptoms, information needs, practical concerns, anxiety or low mood, family anxieties and overall feeling of being at peace. Items in question 2–9 are scored from 0 to 4, and overall scores can range from 0 to 68. Questions 1 and 10 are not scored.			
Patient Health Questionnaire 9^57^		A 9-item instrument developed to screen for major depressive disorder, and validated in palliative care populations.^58^ Items are scored 0 to 3, and it can be scored continuously or with validated cut-offs for mild (5 to 9), moderate (10 to 14), moderately severe (15 to 19) and severe depression (20 to 27).^59 60^ The cut-off for a depression ‘case’ is 10.			
Generalised Anxiety Disorder 7^61^		A validated 7-item anxiety screening instrument that is used to screen for anxiety in palliative care settings. Items are scored 0 to 3, and total scores range from 0 to 21. Severity of anxiety symptoms can be classed as none (0 to 4), mild (5 to 9), moderate (10 to 14) or severe (15 to 21). The cut-off score for a generalised anxiety disorder ‘case’ is 10.			
Single-item Sleep Quality Scale^62^		A short, pragmatic, tool for assessing sleep quality that has been validated in people with insomnia and depression, selected to reduce burden on participants from lengthier alternatives such as the Pittsburgh Sleep Quality Index.^63^ A single Visual Analogue Scale asks respondents to rate their overall quality of sleep over the last 7 days on a scale of 0 to 10. Scores are used to categorise sleep quality as: terrible (0), poor (1 to 3), fair (4 to 6), good (7 to 9) and excellent (10).			
Uptake of existing mental health services		A 3-item form developed by our research team specifically for this study asking participants if they have ever (a) sought help from a healthcare professional for their mental health; (b) sought help from a healthcare professional for their mental health over the past 2 weeks; and (c) any plans to seek help from a healthcare professional for their mental health in the future. Response options are ‘yes’, ‘no’ or ‘prefer not to say’.			
Meaningfulness/ personal/mood ratings	Immediately after each expression session	A 3-item, 7-point Likert scale based on a measure used in a study testing a similar intervention,^64^ measuring how personal and meaningful participants’ felt their expression session was (not very personal/not very meaningful (−3) to (+3) very personal/very meaningful). The last item will be a mood check where participants are asked to rate how they feel on a 7-point scale (very sad (−3) to (+3) very happy).	Quantitative	Descriptive statistics	Feasibility and acceptability Impact on well-being Outcome measure selection Underlying mechanisms
Feedback form	Immediately after final expression session	Participants will be asked to complete an online feedback form exploring their experience of completing the intervention, if they needed any assistance from a carer and the nature of that assistance, and their fidelity to the protocol. The feedback form questions were informed by work on ethical research in vulnerable populations^65^ and the theoretical framework of acceptability for healthcare system interventions.^53^	Quantitative and qualitative	Descriptive statistics and combined deductive and inductive thematic analysis	Feasibility and acceptability Impact on well-being Outcome measure selection Underlying mechanisms
Semi-structured interview	Within 8 weeks of final expression session	Exploring participants’ experience of the intervention and questionnaires, including whether they experienced any negative feelings during or after each expression, whether they found the intervention helpful and the appropriateness and relatability of the expression session prompts, expanding on the topics covered in the feedback form	Qualitative	Combined deductive and inductive thematic analysis	Feasibility and acceptability Impact on well-being Outcome measure selection Underlying mechanisms

*All measures will contribute to the primary objective: optimisation of the intervention as informed by a process evaluation (see table 3).

BIR, blinded independent review; LIO, let it out; LIWC, linguistic inquiry word count.

#### Expression sessions—group 1

Over the 2-week intervention period, participants will type, handwrite or audio-record (format chosen by the participant) their response to the three prompts. Handwritten and audio-recorded responses will be transcribed for analysis. It is not mandatory for participants to share their expression session responses if they would prefer to keep them private. Methods for data collection and transfer are summarised in table 2. Researchers will contact each participant by phone or email (participant preference) at the end of the first and second week of the intervention to check on their well-being. If during contact with the participant the research team suspects they may no longer have capacity for informed consent, or is experiencing severe distress, the hospice clinical team will be informed and capacity formally assessed. If the participant is deemed no longer eligible to take part in the study, they will be withdrawn and the directives from their advance consent form followed.

**Table 2 T2:** Methods of expression session data collection and transfer for Group 1 participants

Method of disclosure	Data collection	Method for transfer to research team
Typed into platform	Participant types directly into text box on online survey platform (Research Electronic Data Capture [REDCap] via Data Safe Haven).	Research team have access to data entered onto REDCap via Data Safe Haven.
Typed on device	Participant types into word processor on own device.	Participant saves file on own device and uploads it to the REDCap via Data Safe Haven survey platform.
Handwritten	Participant handwrites responses on own paper.	Participant takes photo of handwritten responses using mobile phone camera and sends via WhatsApp to research team* (end-to-end encryption). Photos transferred to Data Safe Haven and deleted from phone.
Audio-recorded on smart phone	Participant records themselves using either inbuilt recording/notes application on their phone or the Rev application (free to download).	Participant sends audio-recording via WhatsApp to research team* (end-to-end encryption). Audio-recording transferred to Data Safe Haven and deleted from phone.
Audio-recorded on laptop/computer	Participant records themselves using free Audacity software.	Participant saves file on own device and uploads it to the REDCap via Data Safe Haven survey platform.

*The research team will have a dedicated study phone that a member of the research team keeps only on their person during working hours (09:00–17:00 Monday–Friday) and is kept in a secure locked cabinet outside of those hours. The phone will be checked once a day for recordings or photos received, at which point the recording will be transferred to the dedicated project file on Data Safe Haven and deleted from the phone.

#### Self-report measures—group 1

All self-report data is collected online using the Research Electronic Data Capture (REDCap) online survey platform.^47 48^ Group 1 participants will complete a demographics questionnaire at baseline (prior to receiving the intervention). They will also complete a series of health-related questionnaires at baseline and 1, 4 and 8 weeks after the final intervention session (secondary outcome measures). Group 1 participants will also be prompted to log in to the platform during or after each expression session to indicate they have completed the session, and (if they wish) to share their response with the research team. Directly after each expression session they will also be prompted to complete a short self-report questionnaire to monitor their mood, and perception of how meaningful and personal the session was (secondary outcome measures). After the final expression session, participants will also complete a feedback form (primary outcome measure).

#### Semi-structured individual interviews (primary outcome measure)—group 1

Semi-structured interviews (n≤15) will be conducted within 8 weeks of the participant’s final expression session. Interviews will be conducted by DM, following a topic guide to explore participants’ experience of the intervention and questionnaires, including whether they experienced any negative feelings during or after each expression, whether they found the intervention helpful and the appropriateness and relatability of the expression session prompts, expanding on the topics covered in the feedback form.

Interviews will take place virtually and will be audio-recorded using Microsoft Teams, to minimise face-to-face interactions in line with government COVID-19 guidance. Recordings will be transcribed verbatim for analysis; transcripts will be pseudonymised and personally identifiable information redacted from the transcript.

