##### Impact on psychological and physical well-being

Inductive thematic analysis of interviews and feedback from free-text responses from patients, carer and staff participants. DM will develop codes from the raw data, to be checked and adjusted by the research team; data will be re-coded, checked and adjusted until code saturation is reached.Descriptive pre–post analysis of changes in outcome measures (Integrated Palliative Care Outcome Scale, Patient Health Questionnaire 9, Generalised Anxiety Disorder 7, Sleep Quality Scale, uptake on mental health services): mean and standard deviation of scores at each time point.Descriptive summary of number of adverse effects reported by clinical team and participants.

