##### Choice of outcome measure

Inferences of potentially suitable outcome measures will be based on results from descriptive pre–post analysis of outcome measures, and qualitative analysis of interviews and feedback from free-text responses from patients, carers and staff participants regarding reported impact of the intervention.

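### The only IPOS score the article describes is a 0–68 total that cannot separate physical from emotional change; summaries by content group should stand beside it

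*Protocol article*

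**What the plan says.** Table 1 of the protocol article (Data collection) introduces IPOS as "An updated, brief (10 questions, 17 items) version of the POS instrument" and describes its content as "covering symptoms, information needs, practical concerns, anxiety or low mood, family anxieties and overall feeling of being at peace". On scoring it says "Items in question 2–9 are scored from 0 to 4, and overall scores can range from 0 to 68" and "Questions 1 and 10 are not scored". No subscale, domain score or item-level summary of IPOS is named there or elsewhere in the article.

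Under Impact on psychological and physical well-being, IPOS is listed with the PHQ-9, GAD-7, sleep scale and service-uptake form. The summary for all of them is "mean and standard deviation of scores at each time point".

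The objective served is "Explore the potential impact of the intervention on psychological and physical well-being, and identify any potential adverse effects" (Aims and objectives). The same results have a second use. Under Choice of outcome measure, "Inferences of potentially suitable outcome measures will be based on results from descriptive pre–post analysis of outcome measures", together with qualitative analysis of reported impact.

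**The concern.** The objective names two kinds of well-being, and Table 3 asks about change in psychological and in physical health measures. The IPOS total sums across both, so its mean cannot show which one moved.

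The exposure is uneven:

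- **Physical symptoms.** Apart from the single sleep item, no other scheduled questionnaire is described as covering them. If only the total is summarised, the physical half of the objective has no clean quantitative answer.
- **Family anxiety and peace.** Table 1 attributes these to IPOS and does not describe the PHQ-9 or GAD-7 as covering them. Peace lies close to the comfort and acceptance that the intervention is meant to bring, and a change there would be diluted in a 17-item sum.
- **Depression and anxiety.** These are already summarised separately and do not depend on the IPOS total.

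The setting makes opposite movements plausible. Participants are terminally ill, a 2-week intervention is followed up to 8 weeks after the last session (about 10 weeks in all), and there is no comparator arm. A flat total could then count against IPOS as a future outcome measure although one part of it had responded.

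**Working it through.** **Inputs from Table 1.** 17 items; questions 2 to 9 scored; each item 0 to 4; questions 1 and 10 unscored; stated overall range 0 to 68.

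**Step 1: reproduce the stated range.** Minimum 17 × 0 = 0; maximum 17 × 4 = 68. The stated range is correct, and it uses all 17 items.

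**Step 2: what a change in the total can show.** Change in total = change in symptom items + change in all other items. Assume that all items are scored in the same direction, with higher meaning worse; the article does not state the direction.

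| Change in other items | Change in symptom items | Change in total |
|---|---|---|
| −4 | 0 | −4 |
| −4 | +2 | −2 |
| −4 | +4 | 0 |
| −4 | +6 | +2 |

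A total change of 0 is compatible with no change anywhere and with two real changes in opposite directions. This needs no assumption about how the 17 items divide. The sizes are illustrative and are not taken from the article.

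**Step 3: how much weight symptoms carry.** The article does not give the split. Questions 2 to 9 are 9 − 2 + 1 = 8 questions holding 17 items. If one of them is a multi-item symptom list and the other seven are single items (assumption), then:

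- symptom items: 17 − 7 = 10, range 0 to 40, share 40/68 = 59%;
- other items: 7, range 0 to 28, share 28/68 = 41%.

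**Step 4: cancelling worsening, over a range of splits.** Suppose that every non-symptom item improves by 0.5. The mean worsening per symptom item that leaves the total unchanged is 0.5 × (other items) / (symptom items).

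| Symptom items | Other items | Symptom share of range | Gain in other items | Cancelling worsening per symptom item |
|---|---|---|---|---|
| 7 | 10 | 28/68 = 41% | 5.0 | 5.0/7 = 0.71 |
| 10 | 7 | 40/68 = 59% | 3.5 | 3.5/10 = 0.35 |
| 12 | 5 | 48/68 = 71% | 2.5 | 2.5/12 = 0.21 |

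The more symptom items there are, the smaller the average decline that hides a given gain elsewhere.

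**Step 5: compare with the other scales in Table 1.** The PHQ-9 is given a continuous score, severity bands and a case cut-off. GAD-7 has bands and a case cut-off, and sleep has five categories. IPOS, which has the most mixed content of the four, has only the total.

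**The case against.** The strongest reply is that this infers a plan from silence. The 0–68 sentence stands in the description column of Table 1 and tells the reader how the instrument is scored. The analysis text speaks of scores for five measures together and excludes nothing. A journal article condenses, and domain summaries may well be set out in a fuller document. This stands in part: a reader might infer that the total is the sole IPOS summary planned, but the article never says so. What can be said is that it is the only IPOS score described, although Table 1 does find room for alternative scorings of the other scales.

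A reader might also infer that the study cannot answer the psychological question, or that emotional harm would go unseen. The article does not support either. The PHQ-9 and GAD-7 are summarised separately, mood is rated after each session, researchers check on well-being at the end of both intervention weeks, interviews ask about negative feelings, and adverse effects are counted.

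Three further replies have force. The study tests no efficacy hypothesis and reports no p-values, so cancellation cannot produce a wrong test decision. Outcome choice also draws on qualitative data, so nothing says that IPOS will be judged on its total alone. The article gives no expected rate of symptom worsening, and the worked examples show that cancellation is possible, not that it is likely. Finally, with one arm, domain scores would still mix disease course with any intervention effect. Splitting the score shows where change occurred, not why.

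None of this lets the total itself separate physical from emotional change, or supplies another questionnaire described as covering physical symptoms beyond sleep.

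**Conclusion.** The point holds as one of interpretability and is minor to moderate. As described, the IPOS total cannot distinguish physical from emotional movement, and its mean at each time point should not be read as evidence of stability in either. The consequence falls mainly on the physical half of the impact objective, on family anxiety and peace, and on the pre–post evidence used to choose outcome measures.

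The 0–68 range is not an error, and the plan does not contradict itself here. That opposite changes can cancel is arithmetic, given items scored in one direction. How much cancellation to expect is unknown: the symptom share of 41% to 71% rests on assuming 7 to 12 symptom items, and worsening of symptoms over follow-up is a reasonable inference from the population, not a figure in the article.

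**What to change.** In the IPOS row of Table 1 and under Impact on psychological and physical well-being, state that IPOS will be summarised by content group beside the overall total, with mean and standard deviation at each time point. Suitable groups are symptoms; emotional, family and peace; and information and practical concerns. If the instrument has an established domain grouping, use that one, and name it before the data are examined. Read the symptom group for physical impact. Read the emotional, family and peace group alongside the PHQ-9 and GAD-7 for psychological impact.

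Under Choice of outcome measure, add that the suitability of IPOS for a future evaluation will not be judged on the total alone.

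The cost is a few descriptive rows per time point from items already collected. There is no added burden on participants and no change to the sample size or schedule.
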